### Data collection

#### Quantitative approach

The data collection method will include regular follow up with community health workers and questionnaires. The number of women using transportation vouchers and the cost will be verified and recorded. All vouchers will be distributed and reimbursed electronically. All costs will be retrieved, and at the end of the study, the health economist in the study will assess the cost. A review of each clinic visits and assessment of compliance (e.g., antenatal care attendance, communications with communications, communications with physicians using mobile phones for follow up, and reminder text messages) will be assembled by the main project lead and research coordinator during the study.

#### Outcome measures

All outcomes will be assessed by self-reports, objective assessments, and face-to-face interviews. The clinical outcomes in Table 1 will be collected objectively by providers directly on the PNMS platform as participants attend their antenatal care visit, and they will also be collected from self-reports by data collectors as follows. All participants in the intervention and control groups will be assessed at the following time points: baseline (T0) at recruitment into the trial, midpoint (T1) at 32 weeks into the trial and endpoint (T2), which is immediately after delivery. For the postnatal period, 2 months immediately after delivery (post-intervention period), data will be collected solely on exclusive breastfeeding, which is at T3 (2 months after delivery). At each time point, participants will be asked the same set of questions plus repeated questions on antenatal care visit, skilled delivery and family planning. Baseline measures will include sociodemographic data on age, gender, income, education, marital status, place of residence, religion, and occupation.

The study timeline is outlined in Table 2, adapted from the Standard Protocol Items: Recommendations for Interventional Trials (SPIRIT) template [51], and data for the tertiary outcomes will be collected at the following time points: T0, T1, T2, T3, as defined above.

**Table 2 Tab2:** Schedule of enrolment, interventions, and assessments in accordance with activities on WHO focused ANC package

TIMEPOINT^a^	June to August 2018	Study period (September 2018 to September 2019)							
	Formative study	Enrolment	Allocation		Post-allocation				Postnatal and Close-out
	Phase I		t0 (Baseline)	(ANC #1 (8–12 weeks)	ANC#2 (24–26 weeks)	t1 (ANC# 3 (32 weeks)	ANC#4	t2 Delivery	t3 Postnatal
Key informant interviews and focus group discussions	X								
Enrolment:									
Eligibility screen		X							
Informed consent		X							
Pre-assessment demographics		X							
Allocation			X						
Interventions									
[Group A e-vouchers and mobile phones]				X	X	X	x	X	X
[Group B control, standard care]				X	X	X	x	X	X
Assessments									
[medical history, examination, drug history, malaria/HIV screening, antenatal history, hep B screening, on ARV, preeclampsia, echography/fetal movements]			X	X	X	x	x	X	
[outcomes, #ANC, delivery, MMR,FP]			X		X		X		X
[Exclusive breastfeeding]									X
CHW weekly follow-up			X	X	X	x	x	X	X
Resource utilization and management	x	X	X	X	x	x	x	x	X
Economic analysis									X
Post Intervention FGD									X

Displayed under assessments

^a^List specific timepoints in this row

#### Baseline data for clinical outcomes

After enrolment, data collectors will collect data using a set of questions for both the intervention and control groups. The data collectors are blinded and will not know which area is the intervention area and which is the control area. Data collectors do not live in either the health area or the district and are not aware of the nature of the intervention.

#### Intervention

During the intervention period from October 2018 to September 2019, the following data will be collected: attendance at ANC1, ANC2, ANC3, and ANC4 visits and the timing of these antenatal visits, followed by a list of variables as outlined in Table 2.

Data will be collected at three different levels. At the hospital and/or health center level, data from the intervention group will be collected directly from the mobile web-based version online PNMS, where the doctor will log in to enroll the patients. The questionnaire will contain characteristics of the baseline data and an antenatal focused package. In the control areas, the data will be collected directly from the District Health Information System (DHIS2) as usual. Data collectors will collect data at different times using Magpi, and these data will be triangulated with the data that are collected by healthcare providers and through community health worker weekly follow-ups. The third level of data collection by community health workers will occur on a weekly basis, and this information will be collected using Magpi, which will allow geo-mapping of participants to help control for loss to follow up through displacement. These data will be triangulated for quality and consistency in both the intervention and control areas.

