### Recruitment and follow up

Recruitment into the study will be prospective, and each participant will be followed during their pregnancy until they deliver. Mothers who do not deliver in the hospital will be followed-up in the community by community health workers within 1 week of delivery. The study will run for 18 months to allow time for the outcome to be measured and for enough participants to be enrolled in the study (this includes the formative phase). Recruitment is primarily based on referrals through community health workers, by word of mouth in the community, and through health-educational programs and healthcare workers in respective health clinics. Prior to introducing the intervention, community sensitization and the involvement of village leaders will be carried out in the health areas. Community meetings will be organized to explain the intervention to all community members through a brief pop-up presentation by the project lead and project coordinator. Furthermore, community health workers will be trained to inform all pregnant women about the intervention on an individual basis.

A total of eight community health workers will be involved in the project, two from each health area. Recruitment will occur within 8 months (allowing enough time for all women to deliver within the 18-month study time frame), and each community health worker will be responsible for recruiting approximately 35 pregnant women (approximately five women per month) to attain the estimated sample size. However, these districts have yearly deliveries totaling a minimum of 500 in Bali and over 1000 in the Ndop district [8]. Therefore, the estimated sample sizes are anticipated to be reached within a year. However, considering that all health areas within the district are eligible, the anticipated contingency plan for recruitment will be to recruit individuals from other health areas within the same district or divide the participating district into zones.

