### Intervention and control

i.Intervention

The intervention is a prenatal management system (PNMS), which utilizes pictographs and local dialects by (i) using pictographs that reflect local norms and realities to communicate health needs and concerns, (ii) providing ongoing mobile family planning education in local dialects and sending reminder text messages, (iii) communicating emergencies to providers using geographic information system (GIS) and geo-localization, (iv) increasing access to and utilization of antenatal care and skilled delivery, and (v) integrating this technology into selected district health systems.

Upon registration into the PNMS, pregnant women will be provided five e-vouchers; one e-voucher will be automatically redeemed at each prenatal visit, and the account of the health center will be credited. Mobile phones will be provided to eligible pregnant women, along with electronic vouchers that will be redeemed upon antenatal visits and delivery. Each eligible pregnant woman will be assigned five vouchers (four for antenatal visits and one for delivery, including five transportation vouchers). The vouchers will be administered electronically, and the users of the application will communicate their state of health with providers using graphic signs on their phones or direct calls, which on arrival will be sent to the appropriate health personnel. Messages will consist of both audio and text messages. The health personnel will receive this information on their computers as well as on their phones as SMS alerts and will react appropriately.

Training of healthcare providers and community health workers in using the PNMS and training of pregnant women on how to use the features of the mobile application, including the GIS feature during emergencies, will be provided. The proposed interventions (e-vouchers and mobile phone application) are noninvasive and impose no direct adverse effects on the participants. Every woman is assigned a code to her profile that identifies her upon each visit. There are six graphical icons embedded within the app that indicate the following categories: pain, emergency, family planning, antenatal care, medical advice, and postnatal care.

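### The printed calendar is two months short of the stated 18 months and closes before some women recruited over 8 months would deliver

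*Protocol article*

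**What the plan says.** **Duration.** Recruitment and follow up states that "The study will run for 18 months to allow time for the outcome to be measured", and adds that this includes the formative phase. It continues: "Recruitment will occur within 8 months (allowing enough time for all women to deliver within the 18-month study time frame". Each woman is followed through pregnancy to delivery. The same section later says that "the estimated sample sizes are anticipated to be reached within a year".

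**Dates.** The Table 2 header places the formative phase in "June to August 2018". It places everything from enrolment to postnatal close-out under "Study period (September 2018 to September 2019". The Intervention paragraph of Data collection lists the data gathered "During the intervention period from October 2018 to September 2019".

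**Gestation at entry.** The eligibility criteria allow entry up to 4 months. Table 2 puts the first antenatal visit, after allocation, at 8–12 weeks.

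**After delivery.** Outcome measures reads "For the postnatal period, 2 months immediately after delivery (post-intervention period" and restricts data collection at that point to exclusive breastfeeding. Table 2 nevertheless marks Group A (e-vouchers and mobile phones) at t3, and the app's icons are "pain, emergency, family planning, antenatal care, medical advice, and postnatal care".

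**The concern.** The 18-month duration is the protocol's own justification for 8 months of recruitment. If the calendar is really 16 months, that justification fails, and some late-enrolled women are still pregnant at the printed close.

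Delivery matters here. One of the five vouchers is for delivery, skilled birth delivery is a listed clinical outcome, and t2 is set immediately after delivery. A team working to the September 2019 date could miss delivery data on late enrollees. A team working to follow-up until delivery would run past the date printed for both the study and the intervention. The text does not settle which governs. It is also unclear whether the intervention is still in place between delivery and t3.

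**Working it through.** **1. The plan's own figure.** Formative phase, June to August 2018: 3 months. Study period, September 2018 to September 2019: 13 months. Total 3 + 13 = 16 months, against 18 stated. Eighteen months from 1 June 2018 would end on 30 November 2019.

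**2. Last deliveries.** Inputs from the protocol: 8 months of recruitment (about 243 days) and entry at 4 months or less (about 17.4 weeks). Assumptions, because the protocol does not give them: recruitment starts on 1 September or 1 October 2018, accrual is even, delivery is at 40 weeks, and the earliest entry is at 8 weeks.

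Time left at entry is 7 × (40 − g) days, for g weeks' gestation:
- g = 17.4: 158.2 days
- g = 12: 196 days
- g = 8: 224 days

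The last woman, enrolled on day 243, delivers on day 401 (g = 17.4) to day 467 (g = 8). From 1 September 2018 that is 7 October to 12 December 2019. From 1 October 2018 it is 6 November 2019 to 11 January 2020.

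**3. Share undelivered on 30 September 2019.** Let A = 243 and let C be the days from recruitment start to the end of 30 September 2019 (395 for a September start, 365 for October). Then share(g) = [A + 7(40 − g) − C] / A.

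| Gestation at entry | September start | October start |
|---|---|---|
| All at 17.4 weeks | 6.2/243 = 2.6% | 36.2/243 = 14.9% |
| All at 12 weeks | 44/243 = 18.1% | 74/243 = 30.5% |
| All at 8 weeks | 72/243 = 29.6% | 102/243 = 42.0% |
| Even over 8–17.4 weeks | 39.1/243 = 16.1% | 69.1/243 = 28.4% |
| Even over 8–12 weeks | 58/243 = 23.9% | 88/243 = 36.2% |

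The share is linear in g, so each "even" row is the mean of its two end values. Counting the close at the start of 30 September takes one day off C and makes the last cell 89/243 = 36.6%. Hence about 3% to 37% across the patterns with entry at the limit or spread over a range.

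**4. Sensitivity to the recruitment period.** With recruitment complete in 6 months (A = 182.5) and entry at 8–17.4 weeks, the share falls to about 0.6% (September) and 7% (October). With 12 months (A = 365) it runs from 128.2/365 = 35% (September, all at 17.4 weeks) to 191.1/365 = 52% (October, 8–17.4 weeks).

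**5. An 18-month close, 30 November 2019.** C becomes 456 or 426. Entry at 8 weeks then overruns by e = 467 − 456 = 11 days or 467 − 426 = 41 days. The overrun reaches zero before 17.4 weeks, so over 8–17.4 weeks (65.8 days) the share is e² / (2 × 243 × 65.8):
- September start: 121/31,979 = 0.4%
- October start: 1,681/31,979 = 5.3%

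The 18-month claim is therefore nearly true of an 18-month calendar that starts recruiting in September. It is not true of the dates printed.

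**The case against.** **The dates bound data collection, not service.** The sentence with the October 2018 to September 2019 window sits under Data collection and lists what is recorded. Vouchers are assigned per woman with no expiry, the emergency feature has no end date, and follow-up runs to delivery. This stands. A reader might infer that delivery vouchers and emergency response are withdrawn while women are still pregnant, and that women are left with icons nobody answers. No section says so, and close-out arrangements may sit in a fuller document. What remains is that the text calls the window the intervention period and Table 2 gives the same end.

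**The share rests on unstated inputs.** This also stands. Eight months is a ceiling, and faster recruitment shrinks the share. With whole-month counting and a 9.0-month pregnancy, a September start with every woman at the 4-month limit just fits: 3 + 8 + (9 − 4) = 16. That fit has no margin and needs every woman at the limit.

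**Dilution of the effect.** A reader might infer a biased intention-to-treat comparison. The pilot is about feasibility, its clinical outcomes are described as planned for the larger study, and Table 1 only summarises them. Capture of delivery data and consistency of the timetable are the firmer reasons to act.

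**The t3 mark.** The control row carries the same mark, so it may only show arms under observation. That makes the period after delivery unclear rather than plainly contradictory.

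**Conclusion.** The point holds as an inconsistency of dates. The printed calendar spans 16 months, not 18, and at 40 weeks' gestation the last women recruited in month 8 deliver after it closes, by about a week in the most favourable case and by some ten weeks for entry at 8 weeks (September start).

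Under even 8-month accrual and entry at 8–17.4 weeks, about 16% to 28% would be undelivered on 30 September 2019. The start date and gestation at entry drive the 3% to 37% range, and neither is given. Counts depend on the arm size, which the Sample size section leaves unclear: about 11–20 women if the intervention group is 70, or 22–40 if it is 140.

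The documents do not establish that any service stops at the close. They leave open whether the intervention period covers these deliveries and what applies between delivery and t3. This should be corrected, but it is not of the first rank.

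**What to change.** Reconcile Recruitment and follow up, Table 2 and the Intervention paragraph of Data collection to one set of dates, and state the recruitment start. There are two routes:

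- **Correct the close** to a date that covers the last expected delivery. November 2019 is enough for a September start but leaves about 5% undelivered for an October start. If the close is meant to include t3, it must fall two months after the last delivery.
- **Keep September 2019 and state a last-enrolment date.** Counting back from 30 September 2019, a woman at 17.4 weeks must enter by about 25 April 2019 (158 days) and a woman at 8 weeks by about 18 February 2019 (224 days). A single February cut-off shortens a September-start recruitment window from 8 months to about 5.6 (170 days), so 280 women would need about 50 a month instead of 35.

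Also reconcile the sections on what applies to women still pregnant at the end date, and between delivery and t3. Which service rule applies is for the investigators.

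The first route costs a change of dates and, for a September start, about two more months of follow-up, already within the 18 months stated. The second costs faster recruitment or fewer women.

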## Data management

Once data are collected in Magpi by data collectors and community health workers, the information will be immediately uploaded, and the project coordinator and research assistant will be able to view these data and check for any missing or erroneous data; any queries related to any data will be sent to the project lead to be resolved with the data collectors or community health workers who collected the data.

Attendance at antenatal care and delivery visits will be recorded in the web-based online prenatal system and will be checked online on a weekly basis by the project lead to control for any missing data, and any queries will be resolved by the district supervisor and the provider along with the project lead.

All attendance during the training and workshops, as well as stakeholder meetings, will be recorded in a handwritten format, and after each session, the participants will sign a feedback evaluation form designed specifically for participants attending the training sessions. Attendance during focus group discussions will be similarly recorded by hand, and records will be signed after each session. All key informant interviews and focus group discussion will be recorded with participant consent. Notes during the focus group discussion will be transcribed, and the recordings will be transcribed from pidgin English to standard English. All transcriptions will be checked for quality, and all photographs will be stored in the same package as the transcriptions. Consent forms and paper records will be stored in a locked cabinet in the office of the research coordinator, which has restricted access. All data will be stored in secured databases with restricted access.

One of the research assistants will be responsible for managing the quantitative data that will be analyzed by the statistician, and all data will be assigned a unique code to blind the statistician. Intervention and control areas will be assigned a unique code before making the data available to the statistician.

### Auditing

Regular auditing of the study conduct will be carried out by members of the team to verify whether the participants’ informed procedures have been followed correctly. Observation and assessment of community health worker weekly reports will be performed using a monitoring framework developed by the team, and participant attendance at antenatal care visits, as well as provider activities and supervision, will be monitored. Community health workers will attend group meetings with field coordinators monthly to review recruitment statuses, concerns, or issues brought forth by participants or potential study candidates, as well as other relevant study details. The community health workers will also attend all the workshops designed during the trial period. Problems discussed during these monthly meetings will be addressed appropriately. There are no safety concerns associated with the intervention.

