## Participants

The study is open to women aged 15–49 (with the current report of underage pregnancy ages of < 15, we anticipate adjusting the age to 13–49 years because this age group is not only vulnerable but also at high risk). Participants must also be ≤ 4 months pregnant and fall within the poverty scale of the study. Any comorbidity that is present at the time of the study that has a direct and/or indirect effect on antenatal care or the life of the woman or her unborn child will be treated appropriately as emergencies within the study (in the intervention group). This step will be performed after the randomization of the health areas into intervention and control groups. Participants in both groups will regularly interact with community health workers.

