#### Quantitative

After enrolment, community health workers will follow up with women on a weekly basis. We anticipate that performance bias will be reduced considering that the outcome is objective, and we also anticipate that detection bias will be reduced by blinding the statistician and data collectors. Providers, community health workers, and patients (pregnant women) will not be blinded because this is not possible due to the nature of the intervention. Selection bias will be eliminated through random assignment. Attrition bias may be likely in the control group because women in the control group may want to drop out of the study or refrain from providing or responding to questions during subsequent visits, especially because they will not be provided any mobile phones. To minimize this bias, we will sensitize the community through stakeholder meetings on the importance of the control group to encourage participation. To control for contamination, e-vouchers will be used, as the women will not be able to sell, misplace, or share their vouchers. Additionally, the use of equity scores as a baseline cutoff for rural or remote rural areas will help to control for contamination, as the health areas are far from each other. Prior to enrolment, the community sensitization, stakeholder meetings, and education programs will be performed to help increase compliance in the control group and prevent women from becoming unresponsive during the trial. We anticipate minimal loss to follow up due to the nature of the exposure (pregnancy) and outcome (antenatal care and skilled birth delivery).

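### Community health workers' training, workshops and briefing of women are not separated by arm, and the contamination safeguards do not cover information these workers carry

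*Protocol article*

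**What the plan says.** The workforce covers both arms. Under Recruitment and follow up: "A total of eight community health workers will be involved in the project, two from each health area". Under Participants: "Participants in both groups will regularly interact with community health workers". The Quantitative part of Addressing sources of bias makes this contact weekly after enrolment, and Table 2 shows the weekly follow-up from baseline to the postnatal period.

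Four statements bear on what these workers learn and pass on:
- Auditing, on workshops: "The community health workers will also attend all the workshops designed during the trial period".
- Auditing, on meetings: "Community health workers will attend group meetings with field coordinators monthly to review recruitment statuses, concerns, or issues brought forth by participants".
- Intervention and control, part i, on training: "Training of healthcare providers and community health workers in using the PNMS and training of pregnant women on how to use the features".
- Recruitment and follow up, on what women are told: "community health workers will be trained to inform all pregnant women about the intervention on an individual basis".

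None of the four is restricted by arm.

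The safeguards are in two places. Addressing sources of bias says: "To control for contamination, e-vouchers will be used, as the women will not be able to sell, misplace, or share their vouchers". It adds that the health areas are far apart. The description of the control group says that control women get no phone, have no access to the family-planning and geographic features, and cannot download the app on a phone of their own. Contamination is a primary feasibility outcome, and Table 1 sets its threshold at 10%.

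**The concern.** Randomization by health area is meant to keep intervention content out of control areas. The named safeguards act on two routes: women passing on vouchers or app access, and women from different areas mixing. A third route is not addressed. A trial worker who has been taught the intervention and works inside a control area can talk about it at a weekly visit.

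Parts of the intervention can travel by word of mouth: family-planning education, prompting to attend antenatal visits, and advice on what to do in an emergency. Antenatal visits and family-planning use or awareness are clinical outcomes planned for the larger study. If control-area workers carry this content, control behaviour could move towards the intervention arm. The contamination percentage, which is there to inform the larger trial, would then mix leakage inherent in the setting with leakage caused by how the pilot trained its own staff, and the two could not be told apart.

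**Working it through.** The point rests on no calculated figure in the protocol. The check is a count of workers and a comparison of routes with barriers.

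**1. Workers in control areas.** Inputs: eight workers, two per area (Recruitment and follow up); four clusters (Sample size); one intervention and one control area in Ndop (Stratification and randomization). I assume the same split in Bali. Areas: 8 / 2 = 4. Control areas: 2. Control-area workers: 2 × 2 = 4.

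**2. Reach of one worker.** Each worker recruits about 35 women: 8 × 35 = 280 = 2 × 140, which matches the 140 per arm under Sample size. Control women: 4 × 35 = 140. One worker's share: 35 / 140 = 25%. The 10% threshold is 0.10 × 140 = 14 women, or 14 / 35 = 40% of one worker's caseload.

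The same section also gives 70 per group and 35 per cluster. With 70 control women, one worker has 70 / 4 = 17.5, again 25%, and the threshold is 7 women, again 7 / 17.5 = 40%. The shares do not depend on which total is meant, provided that workers share the women equally.

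These figures show how many women a worker can reach. They are not contamination rates, because a visit as such is not contamination: both arms are visited weekly by design.

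**3. Routes against barriers.**
- Vouchers passed between women: blocked by electronic, non-transferable vouchers.
- App functions, reminders and geo-localization: blocked, since control women have no phone from the trial and cannot download the app.
- Contact between women of different areas: reduced by distance.
- Information, encouragement or family-planning messages spoken by a worker: no stated barrier. Distance does not act here, because the carrier already works in the control area.

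**4. How firmly the text supports each exposure.**
- Workshops: attendance at all of them is stated without distinction of arm. Their content is not stated.
- Informing women: individual briefing of all pregnant women about the intervention is stated. How much is to be told is not.
- PNMS training: not expressly limited to intervention areas, but described in the intervention part.
- Monthly meetings: not stated to be joint across arms.

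The first two items carry the point. The last two support it only as places where the text leaves the matter open.

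**The case against.** Four arguments stand against the point.

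First, a reader might infer that control-area and intervention-area workers sit in the same monthly meetings and are taught the intervention there. The text does not say so. The meetings are with field coordinators, could be held by area, and have an agenda of recruitment and participants' concerns. This argument stands.

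Second, the training sentence comes under the intervention, and in the same breath covers training women to use the app, which can only mean intervention women. It may well describe the intervention arm alone. This stands too, so that sentence is weak evidence by itself.

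Third, the instruction to inform all pregnant women comes in a passage on sensitization and recruitment, and may mean no more than what consent requires. Community meetings also explain the intervention to everyone, so some awareness in control areas is intended. That is a reason to separate knowing about the trial from receiving its content. It does not remove the gap, since nothing limits what control-area workers say.

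Fourth, a reader might infer a large loss of power. If 25% of control women received the full assumed effect, 20% against 35% would become 23.75% against 35%, a difference of 0.75 × 15 = 11.25 points. Power at 160 per arm would fall from about 85% to about 60%, ignoring clustering. The arithmetic is correct, but the documents do not support the conclusion. Full effect would need vouchers, transport and app functions to transfer, and these are blocked. The 160 per arm belongs to the anticipated larger study, and no contamination rate is given.

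It can also be said that splitting sessions by arm is detail an article leaves to the full protocol. The point does not rest on that silence. It rests on what is stated: all workshops, all pregnant women, and a set of safeguards that does not reach this route.

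**Conclusion.** The concern holds in a limited form. Followed as written, the plan sends four control-area workers to all trial workshops, trains them to speak individually to all pregnant women about the intervention, and has them see control women weekly. The safeguards stop vouchers and app functions from crossing over, but not information, antenatal encouragement or family-planning messages carried by these workers. The contamination result could therefore partly reflect the pilot's own arrangements.

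The size of the effect cannot be given. What can be said is that each control-area worker reaches about a quarter of control women, against a 10% threshold, assuming an even share of women per worker and two control areas. No bias of a given size and no power loss is claimed for this pilot. Two things remain unstated: what the workshops contain, and whether meetings join the arms. The change is cheap and worth making in a study that judges feasibility partly on contamination.

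**What to change.** - **Auditing, and Intervention and control:** limit PNMS training and workshops with intervention content to intervention-area workers until control follow-up has ended. Hold any meeting that discusses intervention content separately by arm. Sessions on recruitment, consent and data entry can stay common.
- **Recruitment and follow up:** limit what control-area workers tell women about the intervention to consent-level information.
- **Table 1:** count as contamination any control woman who reports receiving PNMS or app content, including its family-planning messages, from a health worker. Merely knowing that the trial exists should not count. Because data collectors are described as unaware of the nature of the intervention, the question should be worded neutrally and asked identically in all four areas.

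The cost is some duplicated sessions for the coordinators, later training for the four control-area workers, and a short item in an existing questionnaire. The number of participants does not change.
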